### 2.3. Randomization and Trial Intervention

#### 2.3.1. Randomization

The eligible patients will be randomly allocated to either experimental (VEM) or control (TV) arm in a 1:1 ratio stratified by recruiting center (see Figure 1 for the CONSORT flow diagram). The sequence, generated by the Sealed Envelope randomizer is then uploaded in the Research Electronic Data Capture (REDCap) database [19]. Clinicians, physiotherapists, and patients will not be blinded with respect to the interventions because of the intervention’s nature. However, the clinical–functional, neurophysiological, and biological assessments will be performed by examiners who will be blinded to the patient’s treatment group. The statistician in charge of the analysis will also remain blind.

#### 2.3.2. Trial Protocol

After screening for inclusion/exclusion criteria, a patient is enrolled in the trial and the following demographic and anamnestic variables will be collected: age, sex, education; medical history: time post-injury (TPI), etiology, morphometry and location of brain injury by brain CT scan; pharmacological therapy affecting arousal (e.g., neurosedatives); clinical diagnosis of pDoC (i.e., VS/UWS or MCS) or of eDoC according to standardized clinical criteria [1].

Within one week from enrolment (T0), the enrolled patients will undergo clinical-functional evaluations, neurophysiological assessments and serum blood sampling at study entry as described in Table 3 for primary, secondary, and exploratory outcomes. After the entry evaluation (T0), patients will perform a total of 25 (5 per week for 5 consecutive weeks) 30 min VEM or TV sessions in the same period of the day. Both interventions (i.e., VEM and TV) are non-invasive, utilize CE-marked medical devices, and are routinely used in neurorehabilitation practice. The devices comply with the EU Medical Device Regulation (MDR 2017/745).

In each daily session, patients will be gradually verticalized (from supine up to a maximum of 90° upright position), using a combined robotic-assisted tilt table with lower limb mobilization, Erigo^®^ (Hocoma, Volketswil, Switzerland), (VEM group) or conventional non-robotic tilt table (TV group). The robotic device combines verticalization with rhythmic controlled passive alternating loading and unloading of the legs of which protocol (e.g., simple stepping, sinus walking) will be set up depending on the patient’s osteoarticular condition (e.g., range of movement = 45°; pace = 24 steps/min), without functional electric stimulation. Legs stepping movements will be obtained with the rhythmic alternating feet pushing up that will be tailored from complete (100% of assistance) to no (0% of assistance) passive mobilization for each limb according to the patient’s motor and cognitive ability and side effects such as pain (see Appendix A for the list of available tasks). Similarly, patients assigned to the TV group will be gradually verticalized (from supine up to a maximum of 90° upright position), according to the patient’s clinical, motor, and cognitive status, using a traditional tilt table. The verticalization in both arms of the trial, and the stepping frequency, and the percentage of assistance for each leg in VEM, will be tailored based on patients’ vital parameters, tolerance to verticalization, and pain (see outcome measures below). VEM and TV training will be performed with the supervision of a physiotherapist and a physician will be always available in case of emergency. In the robotic arm, blood pressure drops were managed—before tilt reversal—by increasing stepping frequency or encouraging active pedaling in conscious patients. These strategies were not available in the traditional tilt-table group, where blood pressure (BP) recovery relied solely on repositioning.

During each VEM or TV session, BP, heart rate (HR), and oxygen saturation will be monitored throughout the entire session to prevent complications associated with orthostatism (e.g., hypotension and syncope). In unconscious patients, these vital parameters will be continuously monitored. In conscious patients, they will be recorded at each verticalization step or whenever symptoms or clinical signs potentially indicative of hypotension or cardiac rhythm disturbances occur (e.g., reduced arousal, pallor, nausea). An ad hoc checklist (Adverse Events Report) will be used to record the following possible adverse events (AE), which will also be documented in REDCap: (i) orthostatic hypotension, defined as a sustained drop in systolic BP ≥ 20 mmHg or diastolic BP ≥ 10 mmHg within 3 min of tilt angle change, according to the diagnostic criteria established by the American and European Autonomic Societies [20]; (ii) postural tachycardia syndrome, defined as a sustained HR increase ≥ 30 bpm within 10 min of standing, in the absence of orthostatic hypotension [20]; (iii) bradycardia, defined as HR < 50 bpm; (iv) oxygen desaturation < 90%; (v) signs of excessive pain or clinical discomfort, particularly in patients with pDoC (e.g., agitation, self-removal of medical devices, violent or unsafe movements).

To ensure rapid activation of emergency procedures in the event of AE during verticalization, all patients must have a functioning intravenous access to allow prompt pharmacological intervention if needed. Airway suction, oxygen delivery systems, and a crash cart are readily available; physiotherapists are trained in their use. A nurse and a physician are available on the ward for rapid intervention if required. In the event of orthostatic hypotension, the following steps are implemented: (i) immediate return to the previous tilt angle; (ii) if unresolved, return to 0°; (iii) if hypotension persists, the patient is placed in the Trendelenburg position; (iv) if instability continues, pharmacological treatment is initiated under medical supervision via the pre-established IV access.

In addition, we defined a graded framework for AE seriousness and relatedness to guide session management:-Mild AE: No session suspension required. Symptoms are transient and resolve without intervention (e.g., mild and temporary facial pallor without changes in vital signs);-Moderate AE: Interruption of a single session is required. Symptoms resolve within the same day (e.g., oxygen desaturation resolving after endotracheal suctioning);-Severe AE: Permanent discontinuation of treatment is considered in case of repeated or persistent AE unresponsive to intervention (e.g., hypotension not responding to reduction in tilt angle), or based on medical judgment prioritizing patient safety.

AEs will be managed according to the 90/385/EEC and 93/42/EEC regulations.

A concomitant usual care and rehabilitation interventions will continue without restriction for both arms. Regardless of allocation to the VEM or TV group, all patients will carry out the comprehensive rehabilitation program as designed by the participating center for the entire study period. The usual rehabilitation program consists of alternating bed positioning, passive limb mobilization, cognitive training, activities to facilitate recovery of consciousness (e.g., multisensorial stimulation), speech, and swallowing therapy. During VEM in sABI study, clinicians will be asked to exercise caution when prescribing “prohibited” (i.e., not permitted under the study protocol) and “proscribed” medications (i.e., permitted but requiring careful documentation and, when necessary, adjustment in timing or dosage). These medications may compromise safety (prohibited agents associated with orthostatic hypotension), and affect the interpretability of outcomes by influencing cognition, attention, arousal, or consciousness (proscribed medications) [21,22]. A list of contra-indicated medications and/or cautions is reported in the Appendix B. Information on pharmacological treatments will be collected at baseline and at all follow-up time points.

At the end of the fifth week of treatment (T1), and after 1 month from T1 (T2) a clinical–functional and neurophysiological evaluation will be performed. A serum blood sample will be collected at T2 (see Table 3).

Clinical–functional and neurophysiological evaluation will be preferably performed early in the morning, after customary nursing procedures, before the rehabilitation treatment. In case of low vigilance of the patient, the CRS-R arousal facilitation protocol [23] will be administered before the evaluation.

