### 2.6. Statistical Plan

All analyses will be conducted by blinded statisticians. Frequencies (percentages) or mean ± standard deviation will be used for descriptive statistics regarding socio-demographic and clinical variables, as well as for the level of satisfaction with the experimental intervention and the occurrence of side effects.

Given that most outcomes are ordinal or exhibit skewed distributions, we will employ linear or generalized linear mixed-effects models (LMM/GLMM) with appropriate link functions. Ordinal outcomes will be analyzed using cumulative logit mixed-effects models, with random intercepts for patients and for enrolling centers. Continuous outcomes approximately normally distributed will be analyzed with LMM, while skewed continuous outcomes will be modeled with appropriate link functions (e.g., log). All models will adjust for baseline values of the outcome (ANCOVA framework) and include time (T0, T1, T2) and group (VEM, TV) as fixed effects, plus their interaction. Model formulas were defined a priori. The following is an example:logit[P(Y_ij_ ≤ k)] = β_0_ + β_1_Group_i_ + β_2_Time_j_ + β_3_Baseline_i_ + β_4_(Group_i_ × Time_j_) + u_patient(i)_ + u_center(i)_
where u_patient(i)_ and u_center(i)_ are random intercepts for patient and center, respectively.

All analyses will be performed with a two-sided significance level of 0.05. Adjustment for multiple comparisons will be made using Benjamini–Hochberg false discovery rate correction. Statistical analyses will be conducted using R (version 4.4.3; R Foundation for Statistical Computing, Vienna, Austria) or equivalent statistical software. Interim analyses are planned at half of the expected sample for safety outcomes only (i.e., AEs).

Patients violating the VEM-sABI protocol will be excluded from the VEM or TV treatment, but the last clinical observation will be considered for statistical analysis, according to an intention-to-treat approach and a Missing at Random (MAR) assumption inherent to the mixed-model framework. To explore the robustness of the results in scenarios where data may be Missing Not At Random (MNAR), we will conduct pre-specified sensitivity analyses using multiple imputation and, where appropriate, alternative approaches such as joint modeling or delta-adjusted pattern-mixture models.

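### The rules for responding to and grading orthostatic hypotension contradict one another, and because the first response differs by arm, the VEM–TV comparison of hypotension may partly reflect handling.

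*Protocol article*

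**What the plan says.** **Response.** Section 2.3.2 describes the VEM arm first: pressure drops are handled, ahead of any tilt reversal, "by increasing stepping frequency or encouraging active pedaling in conscious patients. These strategies were not available in the traditional tilt-table group". For the conventional table it describes a setting "where blood pressure (BP) recovery relied solely on repositioning". Later in the same section comes one sequence with no arm named: "In the event of orthostatic hypotension, the following steps are implemented: (i) immediate return to the previous tilt angle". It continues through a flat position and Trendelenburg to drug treatment through the intravenous access.

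**Definition.** Orthostatic hypotension is a sustained fall of at least 20 mmHg systolic or 10 mmHg diastolic within 3 minutes of a change in tilt. The definition is the same for both arms and gives no duration for *sustained*.

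**Grading.** One scale serves both arms. Mild: "No session suspension required. Symptoms are transient and resolve without intervention". Moderate: "Interruption of a single session is required". Severe covers repeated or persistent events that do not respond to intervention; permanent discontinuation is then to be considered. Section 2.6 lists a severe event among the protocol violations and says that violators are excluded from the VEM or TV treatment.

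**Role in the trial.** Adverse events are a secondary outcome recorded at each daily session (Table 3). The Discussion expects fewer side effects, hypotension included, with VEM. Section 2.3.1 states that clinicians and physiotherapists are not blinded. Section 2.6 names descriptive statistics for "the level of satisfaction with the experimental intervention and the occurrence of side effects".

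**The concern.** Less orthostatic hypotension is the rationale for the robotic table, so this is the safety result readers will look for first. Its meaning depends on three things: what staff do when pressure falls, what is then written down, and what happens to the patient afterwards. The article gives conflicting instructions on the first and third. On the second, it uses a definition whose key word has no duration.

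If a drop is reversed before it is judged sustained, it may never enter the checklist. The permitted means of reversing it differ by arm, and the people deciding know the arm. Grade matters less for the count, but a severe grade can end treatment and so change how many sessions a patient contributes.

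**Working it through.** The main check is textual; no figure in the plan is at issue.

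**1. First response in VEM.** One statement puts stepping or pedaling before tilt reversal. The other makes tilt reversal immediate and does not exempt VEM. Both cannot come first.

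**2. Last response in TV.** One statement says recovery relied on repositioning alone. The common sequence ends with drug treatment. These do not fit together.

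**3. Grade of a corrected event.** Take hypotension that resolves after one step back in tilt (either arm) or after faster stepping (VEM), with the session continuing.

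| Grade | Requirement | Met? |
|---|---|---|
| Mild | resolves without intervention | no, a corrective step was taken |
| Moderate | session interrupted | no, the session continued |
| Severe | repeated or persistent, unresponsive | no, it responded |

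The event has no grade, yet it is the result the first step of the sequence aims for. The example given for severe is failure to respond to a lower tilt angle. By the VEM-specific text, that manoeuvre comes second in VEM and first in TV.

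**4. Consequence of a severe event.** Section 2.3.2 leaves discontinuation to consideration. Section 2.6 makes it follow from the violation rule.

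**5. From handling to counting.** The threshold is common to both arms. An early reversal can stop a drop from becoming sustained by stepping in VEM, and by tilt reversal in either arm. What matters is the net difference between the arms in uncounted drops.

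**6. Illustration of how sensitive the comparison could be.** The documents give no hypotension rate, so these inputs are assumptions:
- p: true per-patient risk of a drop, equal in both arms, 0.20 to 0.50.
- s: net share of VEM patients with a drop who go uncounted, 0.25 to 0.75, with none uncounted in TV.
- 59 patients per arm (Sample Size section) and two-sided α = 0.05 (section 2.6), as if two proportions were compared. The article names no such test for adverse events.

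Counted risk in VEM is p(1 − s). For p = 0.30 and s = 0.50 it is 0.15, against 0.30 in TV, and the pooled risk is 0.225.
- SE under no difference: √(2 × 0.225 × 0.775 / 59) = 0.0769.
- SE under the counted risks: √((0.30 × 0.70 + 0.15 × 0.85) / 59) = 0.0756.
- z = (0.15 − 1.96 × 0.0769) / 0.0756 ≈ −0.01, so the chance of a nominally significant VEM advantage is about 50%.

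| p | s = 0.25 | s = 0.50 | s = 0.75 |
|---|---|---|---|
| 0.20 | 11% | 33% | 70% |
| 0.30 | 15% | 50% | 89% |
| 0.40 | 20% | 66% | 97% |
| 0.50 | 28% | 81% | 99.6% |

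At s = 0 the chance in that direction is the nominal 2.5%. If TV drops were cut short more often than VEM drops, the bias would run the other way. The table shows only that the result is sensitive to s, which the text does not settle.

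**The case against.** **Different events.** The VEM-specific text might concern falls below the orthostatic hypotension threshold and the common sequence only falls that meet it. That would remove the first-step conflict, but the article does not say so.

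**Treatment effect.** Stepping is the mechanism under test, and its frequency is meant to follow vital parameters. Fewer sustained drops because stepping corrects them is partly the benefit being studied. This stands. It is a reason to keep the event as defined and to add a count that precedes the response.

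**Bias in favour of VEM.** A reader might infer that the arms count different things or that the count favours VEM. The documents do not show this: the blood pressure definition is common, and immediate tilt reversal can shorten a TV drop just as stepping can shorten a VEM drop.

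**Grading and summary rules that differ by arm.** This too might be inferred, but both are written once for both arms. Only the response differs. The grades are stated to guide session management, and no endpoint is built on them, so the gap in grading does not by itself change the hypotension count.

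**No comparative analysis.** Section 2.6 puts side effects under descriptive statistics, which might be read as excluding anything more. It does not say so, and the unit and model for adverse events may be in an analysis plan that is not shown. Their absence is not held against the article.

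**Conclusion.** The point holds as a set of contradictions in a safety rule, with a possible consequence for one secondary comparison. Section 2.3.2 conflicts with itself on the first response in VEM and on the means of recovery in TV. Its grades have no place for hypotension corrected during a continuing session. It also disagrees with section 2.6 on what a severe event triggers.

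That handling may affect the hypotension comparison follows from three stated facts: the permitted first response differs by arm, *sustained* has no duration, and session staff are unblinded. How much it does so, and in which direction, is not established. It depends on whether drops reversed early are logged, and the text leaves that open. The illustration rests wholly on assumed risks and an assumed one-sided loss of events, so it is not an estimate. The primary outcome, LCF rated by blinded examiners, is outside this point. The change is worth making before the safety data are interpreted, including at the planned interim look at adverse events.

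**What to change.** 1. The investigators should reconcile the two response passages and the grading in section 2.3.2 with the violation rule in section 2.6. One response sequence per arm should apply, every hypotension event should have one grade, and a severe event should have one stated consequence. Which clinical rule is right is for them to decide; no view is taken here.
2. State what *sustained* means for the event as defined, and keep that count, because recovery through stepping is partly the device's effect.
3. Add a field to the Adverse Events Report: for each session, whether the 20/10 mmHg threshold was crossed at any recording, entered before and regardless of the corrective action. Log the action taken separately.
4. Compare the arms on that field per session attended, for example with a logistic mixed model with random intercepts for patient and centre, and report the VEM–TV odds ratio with its interval.

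The cost is a protocol clarification, one added checklist field and one model. The article places the adverse event checklist in REDCap but does not say that brief drops or all pressure readings are entered there, so the field should be treated as new data capture. The downside is that brief drops are also counted, so the new measure should stand beside the defined event and not replace it.

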In the rehabilitation phase, the early recovery of the upright position (i.e., verticalization) is crucial to prevent secondary complications due to immobility (e.g., stasis pneumonias, deep vein thrombosis, pressure ulcers) [3], enable the stabilization of the hemodynamic balance [4], promote the cognitive performance improvement (especially vigilance and attention) [5], and to ameliorate the muscular-cutaneous trophism and the control of trunk and limbs. However, the Traditional Verticalization (TV) using a conventional tilt table can be hampered by orthostatic hypotension due to cardiac output reduction because of blood pooling in the lower extremities and/or co-existing central sympathetic system impairment [6]. Since its introduction by Czell in 2004 [7] the tilt table equipped with robotic-assisted lower limbs cyclic mobilization has been proposed as a safe and suitable device for a controlled verticalization to facilitate the adaptation to vertical posture in bedridden patients with brain-injury since the acute phase [8]. A combined assisted lower limbs mobilization can activate the musculo-venous pump that enhances counter gradient venous blood flow return to the right heart from systemic circulation, thus resulting in better cardiac output and lower side effects (e.g., orthostatic hypotension) occurrence [9,10]. However, despite the potential benefits and growing popularity of robot-based rehabilitation [11], no conclusive data on cognitive-motor effects of controlled verticalization in patients with sABI have been found, likely because of the methodological bias of the available clinical trials (e.g., small or heterogeneous cohorts ranging from acute to chronic patients, absence of clear randomization; lack of blinding in outcome assessors [5,8,12,13,14]. To minimize bias due to confounding, the present randomized controlled trial (VEM-sABI) will compare multiple clinical, neurophysiological, and biological effects of combined robot-assisted VErticalization and lower limbs Mobilization (VEM) versus a TV in a large cohort of patients with sABI admitted to multiple post-acute rehabilitation settings. The primary aim of the VEM-sABI study will be to evaluate the efficacy of VEM versus TV in promoting short-term recovery of cognitive functioning in a large cohort of patients with sABI. Secondary aims will be to evaluate VEM vs. TV in: (i) preventing or reducing spasticity; (ii) promoting lower limb movements; (iii) reducing functional disability; (iv) and an additional secondary aim will be to evaluate the usability and safety of the two devices from the professional’s point of view. Exploratory aims will be to evaluate the efficacy of VEM vs. TV in: (i) promoting the recovery of consciousness in patients with pDoC; (ii) preventing clinical complications; (iii) maintaining the possible improvement in clinical–functional measures at 1 month after treatment. Additionally, it is crucial to also investigate the patients’ physiological features (such as neurophysiological indices of brain activity and biomarkers of brain damage and plasticity) to accurately outline patients with higher probability to respond to the treatment and detect sub-clinical outcomes [15]. In this context, additional exploratory objectives of study will be to evaluate the effect of VEM vs. TV on brain functionality and neuronal plasticity.

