## 3. Discussion

Patients with sABI are characterized by high clinical complexity, severe cognitive motor disabilities, and an increased risk of developing clinical complications [42,43,44]. An appropriate and skilled comprehensive rehabilitation intervention can significantly impact clinical outcomes and improve the quality of life of patients and their caregivers [1,2,45,46,47]. An early verticalization can promote patients’ recovery and prevent cognitive-motor disabilities and clinical sequelae [3,4,5]. The present multicenter VEM-sABI study will provide new insights into the still-debated efficacy and usability of a device considered safer for verticalization of patients with sABI because it combines robotic verticalization with lower limb mobilization [12]. The study aims to achieve several outcomes. Firstly, it is expected to enroll a large and homogeneous cohort of patients with sABI admitted to post-acute rehabilitation settings. This goal could minimize the methodological bias of the available literature on this field, which most often involved small and heterogeneous patient cohorts (e.g., chronic patients with sequelae of sABI) [5,8,12,13,14]. In addition, we planned to specifically address this topic in post-acute rehabilitation, where the likelihood of patient clinical improvements due to neuroplasticity [18] and the occurrence of clinical complications are higher [42,43,44]. Moreover, we expect that the two cohorts of patients allocated in the experimental and control arm will not differ in terms of demographic and anamnestic characteristics, to avoid biases in evaluating efficacy and usability of the two treatments. Conversely, differences in clinical characteristics and cognitive functions between patients with pDoC and those eDoC are expected. For this reason, targeted clinical and neurophysiological measures will be adopted to detect specific changes in outcome as a function of clinical diagnosis and to identify patients’ profiles with high probability to respond to both (or at least one of the two) treatments. Additionally, we expect the following study outcomes from the data analysis: (i) an improvement of cognitive levels, disability, and motor function at the end of the treatment in both arms, with a significant recovery in the VEM group, in accordance with previous studies [14]; (ii) a more consistent improvement of lower limb strength, and higher reduction in spasticity in the VEM group because of combined controlled mobilization in the VEM device; (iii) lower occurrence of side effects (e.g., orthostatic hypotension) and related dropouts in the VEM arm; (iv) higher occurrence of discontinuation of verticalization due to “treatment futility” in the eDoC patients, as they are more susceptible to early regain vertical posture and gait. A further analysis of motivations of dropouts will identify clinical profiles of patients who could better match the robotic (VEM) or the traditional tilt table treatment (TV); (v) a reduction in clinical complications occurrence in both groups, based on the potential impact of verticalization on patients overall clinical stabilization [3,4]. Because most participating centers are not familiar with this robotic technology in rehabilitation of patients with sABI, we expect to see higher therapist’s compliance for traditional tilt table (i.e., higher SUS score), especially in the early stages of the study. A preliminary structured 3-day training provided by the robotic device manufacturer, on the appropriate use of the robotic device, including real-life testing on at least two different patients, will be performed to avoid potential challenges and ensure the homogeneity in the device use. To ensure ongoing protocol fidelity and inter-site consistency, we implemented the following measures: (i) competency checklist for certification to assess each operator’s ability to manage setup, tilt procedures, stepping control, safety monitoring, and patient interaction; (ii) monitoring parameters (stepping frequency, tilt parameters, adverse events). Ongoing technical and clinical support, throughout constant availability via phone calls and monthly video-call meetings, will be further provided by the coordinator to address possible concerns. We also forecast to identify changes in neurophysiological indices (as measured by EEG) and blood-biomarkers of brain plasticity in patients who will present clinical improvements. In addition, we hope that neurophysiology and biomarkers can detect any sub-clinical (para-clinical) changes caused by the two verticalization procedures. Thus, the two outcome measures will be able to provide useful information to identify patients with a high probability of response to verticalization and help clinicians plan the most appropriate and personalized treatment in such a specific population of patients with sABI.

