Age between 18 and 75 years; sABI due to traumatic, vascular, anoxic, or mixed etiology; Stable behavioral/cognitive diagnosis on at least 4 behavioral evaluations in 1 week using the Italian version of the CRS-R in patients with pDoC, or the LCF-based cognitive assessment in patients with eDoC; Time post-injury between 28 days and 6 months [1]; Not recovered upright station; Written informed consent by the patient’s legal representative/primary caregiver.	Severe medical conditions hampering verticalization (e.g., severe hypotension or conditions realizing hemodynamic instability, end stage or severe symptomatic heart failure with reduced ejection fraction, cardiac arrhythmia of new diagnosis or arrhythmic flare, severe hepatic failure, chronic severe lower limb arterio-venous disease, sepsis/septic shock, thrombus venous embolism of new diagnosis, severe autonomic dysreflexia); Severe medical conditions hampering lower limb mobilization (e.g., fractures, heterotopic ossifications); Severe medical conditions impacting EEG activity (e.g., sub-continuous or abundant EEG epileptiform abnormalities); Severe medical conditions influencing consciousness/cognitive status, such as severe hyponatremia or hypoglycemia; Contraindications to the use of Erigo^®^Basic and/or Erigo^®^Pro (Hocoma, Volketswil, Switzerland) as per technical data sheet (see Appendix A); Presence of prohibited drugs (see Appendix B).

Abbreviations: CRS-R = Coma Recovery Scale-Revised; eDoC = emergence from Disorder of Consciousness; EEG = electroencephalography; LCF = Level of Cognitive Functioning; pDoC = prolonged Disorder of Consciousness; sABI = severe Acquired Brain Injury.

**Table 3 jcm-14-06628-t003:** Summary of primary, secondary, and exploratory outcomes and measures.

Outcome	Timing, Measure
Primary outcome: Global cognitive functioning	At T0 and T1: LCF
Secondary outcomes:	
Functional disability Spasticity of lower limbs Muscular strength of lower limbs Functional independence Usability of devices from physiotherapists Adverse events	At T0, T1 and T2: DRS At T0, T1 and at T2: MAS At T0, T1 and T2: MRC. Additional clinical observation of spontaneous or reflex movement to pain stimulation in pDoC patients At T0, T1 and T2: mBI At T1: SUS Each daily session: AER
Exploratory outcomes:	

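### The adverse-event checklist has no item for leg, skin or device-related injury, so harm from the robotic leg mobilization is not separately identified in the AE outcome or the AE-only interim analysis

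*Protocol article*

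**What the plan says.** The Introduction makes it a secondary aim to "evaluate the usability and safety of the two devices". Table 3 lists adverse events as a secondary outcome, measured by the Adverse Events Report (AER) at each daily session. Table 1 schedules the AER in weeks 1 to 5 and also at T1 and T2.

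Section 2.3.2 sets out the content of the AER: "An ad hoc checklist (Adverse Events Report) will be used to record the following possible adverse events (AE". The five items are:

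- (i) a fall in blood pressure after the table is moved: "orthostatic hypotension, defined as a sustained drop in systolic BP ≥ 20 mmHg or diastolic BP ≥ 10 mmHg within 3 min of tilt angle";
- (ii) a rise in heart rate: "postural tachycardia syndrome, defined as a sustained HR increase ≥ 30 bpm within 10 min of standing";
- (iii) bradycardia, by a heart-rate threshold;
- (iv) desaturation, by a saturation threshold;
- (v) signs of marked pain or discomfort, with behavioural examples for patients with a prolonged disorder of consciousness (pDoC).

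The same section describes what VEM adds to tilting: "rhythmic controlled passive alternating loading and unloading of the legs". Table A1 gives a stepping range of 8 to 80 steps per minute. Table 2 excludes "Severe medical conditions hampering lower limb mobilization (e.g., fractures, heterotopic ossifications", and section 2.3.2 sets the stepping according to the patient's osteoarticular condition and adjusts it for pain.

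Section 2.6 states: "Interim analyses are planned at half of the expected sample for safety outcomes only (i.e., AEs". The Discussion expects "lower occurrence of side effects (e.g., orthostatic hypotension) and related dropouts in the VEM arm".

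**The concern.** A comparative safety outcome should have a place for the harms each arm could plausibly produce. Both arms are tilted; only VEM adds robotic stepping, over 25 sessions. The form names the haemodynamic events that the added stepping is meant to prevent, but nothing mechanical that it might cause. Section 2.3.2 also describes raising the stepping frequency in VEM when blood pressure drops. Handling a listed event can therefore increase exposure to a hazard that has no item. That is a remark about measurement, not about the clinical rule.

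Two uses of the data are at stake. A statement that VEM is as safe as or safer than TV would rest on a list tilted towards events where VEM is expected to do well. And an injury signal in VEM might not appear in the only planned interim safety tables.

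**Working it through.** The protocol states no injury rate and no figure for AE coverage, so there is nothing to reproduce. The check is a reading of every route by which harm could be recorded, followed by a short calculation of what an added item could show.

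**1. Could a leg, skin or device-related injury enter each AER item?**

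| Item | Basis | Would such an injury register? |
|---|---|---|
| (i) orthostatic hypotension | blood pressure after a tilt change | no |
| (ii) postural tachycardia | heart rate on standing | no |
| (iii) bradycardia | heart-rate threshold | no |
| (iv) desaturation | saturation threshold | no |
| (v) pain or discomfort | observed behaviour | indirectly, if it causes visible signs; type and cause not recorded |

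None of the five items names such an injury; one of the five could register it indirectly.

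**2. Where the AER goes.** It is the only stated measure of the AE outcome (Table 3), and the interim analysis is limited to AEs (section 2.6). It is already scheduled at T1 and T2 (Table 1), but four of its five items are vital-sign events, so at those visits it has little to say about a delayed injury.

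**3. Other routes in the protocol.**

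| Route | When | Limit for this purpose |
|---|---|---|
| VAS or NCS-R | each session | exploratory; scores pain, not injury |
| FDG-CCS | T0, T1, T2 | exploratory; general complications, outside the AE-only interim |
| Mild/moderate/severe grading (section 2.3.2) | when an AE occurs | can reach events off the list, but the grades shown describe severity and session handling, with no injury category |
| Protocol-violation reasons (section 2.6) | when they occur | severe cases only |

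**4. What an added item could show.** Inputs: 59 per arm (Sample Size section). The interim is at half of 118, that is 59 patients, or about 30 in VEM. Per-patient injury rates p are assumptions. The chance of at least one recorded event is 1 − (1 − p)^n.

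| Assumed p | n = 30 (interim) | n = 59 (final) |
|---|---|---|
| 1% | 1 − 0.99^30 = 26.0% | 44.7% |
| 2% | 1 − 0.98^30 = 45.5% | 69.6% |
| 5% | 78.5% | 95.2% |
| 10% | 95.8% | 99.8% |

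With zero events, the one-sided 95% upper bound is 1 − 0.05^(1/n): 9.5% at n = 30 and 5.0% at n = 59. These figures assume full recording and no dropout. The listed items alone cannot support such a bound, because a zero would not mean that injury had been looked for.

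**The case against.** The strongest reply is that the AE system is not shown to be closed at five items. The example of a mild AE in section 2.3.2, transient facial pallor, is not on the list, and the severe category leaves room for medical judgment. Severe AEs, transfers to acute wards and missed sessions are protocol violations, so a disabling injury would probably surface, and the Discussion plans an analysis of reasons for dropout. Patients in pDoC have a pain scale designed for them at each session. The article condenses a fuller protocol, whose form may hold an open field.

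Much of this stands, and it limits the point. A reader might infer that the plan cannot see mobilization injuries at all. The documents do not support that, because a painful or severe injury has several ways in. A reader might also infer that such injuries can arise only in VEM. That is not so either: passive limb mobilization is part of usual care in both arms, and the Introduction names heterotopic ossification and pressure ulcers as complications of this population or of immobility. Only the robotic increment is specific to VEM. Nor do the documents show a measured bias towards VEM. Side effects are to be described by frequencies, no composite AE score is defined, and item (v) can count against VEM when stepping hurts.

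What the reply does not remove is this. The article does not leave the content of the form open; it lists it. As listed, a painless or delayed injury has no place in the AE outcome or the interim tables, and a painful one enters without type or cause.

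**Conclusion.** The point holds in a limited form. The AER as listed does not separately identify or attribute lower-limb, skin or device-related injury, and it may miss such injury when it is painless or delayed, especially in pDoC patients. The remaining routes give partial, indirect or exploratory capture. The named items lean towards events VEM is expected to reduce, so the safety comparison is less complete on the side of VEM's added component.

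The size of any effect on the comparison cannot be given: the documents state no injury rate, and any share of missed harms would only restate an assumed one. The conclusion rests on the list in section 2.3.2 being what sites actually complete. If the full form holds more fields, only the article's description needs correction. This should be settled, but it does not threaten the primary outcome.

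**What to change.** Add to the existing AER, identically in both arms, at each session and at the T1 and T2 visits where Table 1 already places it:

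- (vi) new lower-limb musculoskeletal injury;
- (vii) new skin lesion at support or fixation points;
- an open field for other or device-related events.

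Include all three in the secondary AE outcome and in the interim safety tables, and make the AER timing in Table 3 agree with Table 1. If the full AE form already has these fields, correct the list in section 2.3.2 to say so.

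The cost is three fields on an existing form, a minor amendment and slightly longer session paperwork; no new procedure or staff is needed. The gain at the interim is limited: with about 30 VEM patients and an assumed injury rate of 1% to 2%, the chance of seeing any event is only 26.0% to 45.5%. The main benefit is at the final analysis, where zero events among 59 VEM patients would support an upper bound of about 5%.
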